#### **11. Prescriber and Pharmacist perceptions of the two stewardship strategies (Secondary objective 4)**

- Summary tables of # respondents per hospital/period
- Summary of each survey question

#### **12. Resource utilization (cost of antibiotics)**

**Purpose:** to address secondary objective 1, to estimate and compare the resource utilization of each strategy where resource utilization includes cost of antibiotics

To be addressed following discussion of implementation of strategies given drug shortages and pending antibiotics cost information.

#### **13. Patient specific outcomes between each strategy**

**Purpose:** to address secondary objective 3, to compare patient-specific outcomes between each strategy, including but not limited to the following:

494 a. Total hospital days

495 b. Intensive care unit admission

496 Each of Total hospital days, death, and ICU admission will be summarized by hospital in 3 tables:

497 Among admissions with an included antibiotic

498 • Table 1

499 ○ Year prior to study

500 ○ Period 1 Admission with Included antibiotic, no intervention

501 ○ Period 1 Admission with stewardship intervention

502 ○ Period 2 admission with Included antibiotic, no intervention

503 ○ Period 2 admission with stewardship intervention

504 • Table 2

505 ○ Period 1 (all admissions with an antibiotic of interest)

506 ○ Period 2 (all admissions with an antibiotic of interest)

507 • Table 3

508 ○ For 3 contrasts (PAR vs Historical year; Res/PreA vs historical Year; PAR vs Res/PreA)

509 ○ Difference in proportion of ICU admissions with 95%CI

510 ○ Difference in Mean total hospital days with 95% CI

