Stewardship Strategy 2 – Post-antibiotic Review and Feedback. Following approval of the protocol at study hospitals, all prescriptions for targeted antibiotics will be reviewed by the study pharmacist approximately 72 hours after initially written. The clinical pharmacists will review a list of patients receiving the targeted antibiotics on a daily basis to identify patients who have received one or more targeted antibiotics for 72 hours ( $\pm$  24 hours). The pharmacist will review and document the patient's current symptoms, pertinent clinical data, and the indication for the targeted antibiotic documented in the chart. Based on this review, the pharmacist will decide if the targeted antibiotic is necessary and/or if it needs to be modified. If a change is recommended, the pharmacist will then contact the prescriber (i.e., by pager, by phone call, or during clinical rounds) to discuss the pharmacist's recommendations. The interaction will be documented in the REDCap database, including whether or not the prescriber is going to follow the pharmacist's advice. If the pharmacist concludes that the antibiotic is appropriate, then he or she will document that the antibiotic is appropriate but will not be required to contact the prescriber.

Follow up: Strategy 1 and Strategy 2 -- For both strategies, the pharmacist will review the patient's chart approximately five days after interacting with the prescriber to document whether the pharmacist's recommendation was followed. The pharmacist will specifically document if the recommendation was followed, the recommended duration of antibiotic, whether the dose of the antibiotic was appropriate, and the ultimate infection diagnosis. If the patient has already been discharged, the pharmacist will review the patient record to gather this information.

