## 5 STUDY PROCEDURES

### 5.1 Data Collection

- Data will be collected on the following topics:
- Feasibility
- Strategies
  - PharmD chart and prescription review
  - PharmD/Prescriber communication
  - PharmD follow-up
- Pharmacist time
- Pharmacist and Prescriber perceptions (questionnaires)
- Secondary/Exploratory Objectives: DASON database (Pharmacy data, Admit/Discharge Table, Billing ICD9, Microbiology Lab, Bed Flow)
- The PharmD will provide patient data from two time points: first contact and at the time of discharge. In strategy 1, first contact will be the PharmD/prescriber contact and discussion. In strategy 2, first contact will be the date of the PharmD review (approximately 72 hours after the targeted antibiotic was started).

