##### Secondary endpoints (measured at the patient level):

- DOT for each of the targeted and alternative antibiotics
- Duration of hospitalization
- Admission to the ICU (yes/no)
- Duration in ICU
- Discharged vs. death
- Benefit: risk measures to be developed as composites of other outcomes (details provided in an analysis plan)

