## 9.3 Participant Enrollment and Follow-Up

Data from participants admitted to the four hospitals during each of the two six month strategy periods are entered into the database. The data from admission until death or discharge are collected.

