2. Pharmacist time forms - These REDCap forms will be completed by the pharmacist at each hospital and will provide information concerning the time spent on the interventions.
3. Hospital level forms - These REDCap forms will be completed by DASON personnel. These data will include information regarding the approval and implementation of the stewardship strategies at each hospital
4. Questionnaires - These REDCap questionnaires will be completed by the pharmacists and prescribers at each hospital after each strategy is completed (at the end of the six month period). Pharmacists and prescribers will be sent a link to the questionnaires in order to complete. These will not require a REDCap account.
5. Pharmacy data - Antimicrobial utilization data are sent to Duke DASON from each of the study hospitals through routine DASON activities. These data will include PHI such as MRN and dates. These data are created through routine hospital pharmacy activities. These data files will include PHI such as MRN and dates. These data will be transmitted to DUHS via the same sFTP established for routine transmission of data described above. MRN data will not be included in the transfers to DCRI.
6. Bed Flow and Admission-Discharge-Transfer (ADT) data – We will receive bed flow (patient movement within the hospital) and ADT files from study hospitals on a monthly basis through standard DASON activities. These data files will include PHI such as MRN and dates. These data will be transmitted to DUHS via the same sFTP established for routine transmission of data described above. MRN data will not be included in the transfers to DCRI.
7. Demographics data - We will receive data from study hospitals on a monthly basis through standard DASON activities. These data files will include PHI such as MRN and dates. These data will be transmitted to DUHS via the same sFTP established for routine transmission of data described above. MRN data will not be included in the transfers to DCRI.
8. Billing/ICD-9 data - We will receive data from study hospitals on a monthly basis through standard DASON activities. These data files will include PHI such as MRN and dates. These data will be transmitted to DUHS via the same sFTP established for routine transmission of data described above. MRN data will not be included in the transfers to DCRI.

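### ICU admission in SAP 13 has no time origin, so ICU stays at or before the first included antibiotic count as outcomes of the strategy in force

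*Combined protocol and SAP*

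**What the plan says.** Protocol 5.1 lists the secondary endpoint as "Admission to the ICU (yes/no"), at the patient level and with no start time. Protocol 9.3 gives the window of data collection: "The data from admission until death or discharge are collected". SAP 13 restricts the tables with the phrase "Among admissions with an included antibiotic", and its Table 3 gives, for the three contrasts, "Difference in proportion of ICU admissions with 95%CI" and "Difference in Mean total hospital days with 95% CI". Death is to be summarized but has no line in Table 3.

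The strategies act at different moments. For Strategy 1, Protocol 5.1 says "In strategy 1, first contact will be the PharmD/prescriber contact and discussion". For Strategy 2, Protocol 4.1.4 says that prescriptions "will be reviewed by the study pharmacist approximately 72 hours after initially written", with a window of 24 hours either side.

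The data needed to date ICU entry are described. Protocol 16.2 says "We will receive bed flow (patient movement within the hospital) and ADT files from study hospitals on a monthly basis", and Protocol 9.4.2 lists start and stop dates for all antibiotics.

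**The concern.** A patient admitted straight to the ICU and started on an included antibiotic there scores yes, although the ICU entry came before any action under either strategy. The same holds for a patient who spends time in the ICU and receives a first included antibiotic later in the stay.

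ICU admission is one of only two patient outcomes with a planned contrast in SAP 13. Strategy 1 allows a pharmacist to deny a targeted drug, so readers will take this contrast as evidence on safety. Each hospital is to be evaluated separately, and within one hospital strategy and calendar period coincide. A change in the number of patients arriving in the ICU therefore cannot be told apart from a strategy effect in the planned table.

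**Working it through.** **1. Does anything else in the plan supply the time origin?** I looked in five places.
- Patient characteristics (SAP 8): age, race, sex, ethnicity, height, weight and BMI. ICU status is not listed.
- Model in Protocol 9.4.1.3: treatment, period, site, period by site, age, sex and race. There is no severity or baseline ICU term.
- Model in SAP 10: for days of therapy only.
- REDCap table in SAP 9: ICU admission appears under intervention outcome without timing, whereas the neighbouring item on infectious-disease consultation is timed after the intervention. REDCap intervention records cannot cover the historical year or admissions without an intervention.
- Exclusions in Protocol 4.1.2: ICU location is not mentioned.

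So the gap is not filled elsewhere.

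**2. The plan's own figure.** Protocol 9.1 states 97% power for 3000 per period, 0.50 against a difference of 0.05, alpha 0.05. The formula is

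power = Φ{[|p1 − p2| − 1.96·√(2p̄(1−p̄)/n)] / √[(p1(1−p1) + p2(1−p2))/n]}.

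With 0.50, 0.55 and n = 3000: (0.05 − 0.02527)/0.01288 = 1.920, so power is 97.3% two-sided. The stated figure reproduces. No figure is given for ICU admission.

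**3. Assumed inputs.** P is the whole-stay ICU proportion (assumed 0.20; range 0.10 to 0.30). f is the share of ICU patients whose entry was at or before the first included antibiotic (not given; 0 to 0.9 shown). The strategy multiplies later entries only, by an assumed 0.8. n = 3000 is the protocol's figure. It rests on all admissions, and the SAP 13 denominator is a subset, so 1000 is also shown.

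**4. Stable early ICU use.** Whole-stay scoring compares P with Pf + 0.8·P(1−f). Scoring from the antibiotic compares P(1−f)/(1−Pf) with 0.8 times that value, on n(1−Pf) admissions.

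At P = 0.20 and f = 0.5, whole-stay is 10% + 10% = 20% against 10% + 8% = 18%. The 2-point difference is the entire effect on later entries, so the early 10% cancels. The relative effect shrinks: 0.18/0.20 = 0.90. Power is Φ[(0.02 − 0.01985)/0.01013] = 51%. From the antibiotic: 0.10/0.90 = 11.1% against 0.08/0.90 = 8.9%, n = 2700, Φ[(0.02222 − 0.01600)/0.00816] = 78%.

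| f | Whole-stay difference (points) | Whole-stay risk ratio | Power, whole-stay | Power, from antibiotic |
|---|---|---|---|---|
| 0 | 4.0 | 0.80 | 98% | 98% |
| 0.25 | 3.0 | 0.85 | 85% | 93% |
| 0.50 | 2.0 | 0.90 | 51% | 78% |
| 0.75 | 1.0 | 0.95 | 16% | 47% |
| 0.90 | 0.4 | 0.98 | 6% | 21% |

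At f = 0.5 the two powers are 26% and 46% for P = 0.10, 73% and 93% for P = 0.30, and 21% and 35% for P = 0.20 with n = 1000.

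**5. Early ICU use shifts, with no strategy effect.** If early entries rise by a relative r, the spurious difference is P·f·r. With P = 0.20, f = 0.5 and r = 0.20 this is 0.20 × 0.5 × 0.20 = 2.0 points. The standard error is √[(0.20×0.80 + 0.22×0.78)/3000] = 0.01051, and the 95% interval excludes zero with probability 48%. At f = 0.25 and 0.75 the spurious difference is 1.0 and 3.0 points, with probabilities 16% and 81%. A 10% rise at f = 0.5 gives 1.0 point and 16%. With n = 1000, a 20% rise at f = 0.5 gives 20%.

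**The case against.** Five arguments count against the point.

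- **Whole-stay scoring is inferred.** It comes from silence together with the collection window in Protocol 9.3; no scoring rule is stated. That is true. But no other rule is given, and an analyst following the text would score any ICU stay.
- **On the planned scale the effect is not attenuated.** The SAP reports a difference in proportions, and stable early entries cancel in it. This stands: the loss there is in precision, and only the relative effect shrinks.
- **Temporal bias is already admitted.** Protocol 9.4.3 and SAP 3.5.2 call the study essentially non-randomized and warn of temporal effects. Admitting bias does not remove a component that the available dates can separate out.
- **Starting at the antibiotic is not a complete cure.** Under Strategy 2, ICU entries between the antibiotic and the review at 48 to 96 hours still count. Receipt may itself depend on strategy: with 20% ICU, losing 10% of non-ICU recipients alone gives 0.20/(0.20 + 0.80×0.9) = 21.7%. This stands and belongs in the limitations.
- **Only dates are promised, not times.** This also stands, and the rule must deal with same-day events.

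A reader might go further and infer that the contrast mostly measures who was already in the ICU. That needs f above 0.5, and the documents give neither f nor an ICU rate. A reader might also want hospital days counted from the antibiotic. Total hospital days is a named outcome whose plain meaning is the whole stay, so changing it would be a preference and not a correction.

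**Conclusion.** The point holds as a gap in the definition of one secondary outcome, with a practical remedy. ICU stays at or before the first included antibiotic enter the contrast as outcomes. With stable early ICU use the cost is precision: about 51% against 78% power in the central illustration. With shifting early ICU use the cost is bias: 2 points for a 20% relative rise under the same inputs. The 20% ICU rate, the half share of early entries, the risk ratio of 0.8 and the size of the shift are all assumptions, so the actual size is unknown.

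The primary analysis is descriptive feasibility and is untouched. The change should be made because this contrast will be read as safety evidence, but it does not threaten the study's main purpose.

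**What to change.** In SAP 13 Table 3, contrast first ICU entry after the first included antibiotic, among admissions not in the ICU on or before that date. Derive it from the bed-flow/ADT files and antibiotic start dates, with one rule for the historical year and both study periods. Where only dates exist, class same-day ICU entry as baseline. Report ICU stay at or before the first included antibiotic as a baseline characteristic in SAP 8. Keep whole-stay ICU admission alongside as a sensitivity analysis, and leave total hospital days as specified.

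Do not start the clock at pharmacist contact. The historical year has none, its timing differs between strategies, and it would select patients who survive and stay in hospital until contact.

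The cost is SAP wording and one derived variable, after confirming that the historical-year files carry ICU entry dates. The statistical price is fewer ICU events and a smaller at-risk set. State as limitations that the time origin may depend on strategy through antibiotic receipt, and that ICU entries between the antibiotic and the Strategy 2 review still count.
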